Percutaneous transluminal angioplasty (PTA) is usually the first choice of revascularization for the majority of patients with LEAD in the current era. However, intermediate- or long-term prognosis of LEAD patients undergoing PTA remains poor; the average rate of total mortality is 25 % and the average rate of cardiovascular death is 12 % [18–21]. CAD is an independent predictor of total mortality after PTA [18]. Furthermore, ischemia/reperfusion injury after PTA can cause systemic inflammatory response [22, 23], probably leading to peri-procedural cardiovascular mortality in the existence of significant CAD [24]. Interestingly, silent ischemia is common in patients with LEAD because of the high prevalence of diabetes mellitus and inactivity in such patients. A commonly used stress test, the treadmill exercise test, for screening the existence of CAD is usually unsuitable in patients with LEAD because intermittent claudication with resultant limited activity or in bedridden status is frequently present due to severe peripheral artery disease. Furthermore, the accuracy of the available stress tests, including the treadmill exercise test, dobutamine stress echocardiography (DSE), or dipyridamole thallium 201 myocardial perfusion scintigraphy (dTS), is not so high (around 70–75 %), probably hampering vulnerable cases from receiving beneficial revascularization therapy, especially in asymptomatic CAD. Accordingly, prophylactic coronary revascularization may modify short- and long-term cardiovascular outcomes of LEAD patients receiving PTA. However, there is no RCT aimed at the investigation of the prognostic role of routine angiography and revascularization before PTA for LEAD. In addition, it has never been mentioned in the clinical guidelines. Therefore, there is substantial variability in practice strategies among interventionists. Taken together, further investigation of the clinical role of routine screening for the presence of CAD with subsequent revascularization has strong rationality and is deemed mandatory in LEAD patients undergoing PTA.

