### Data collection and outcome measurement

The minimum follow-up period is 1 year and the maximum is 3 years. Clinical outcomes are obtained by chart review if the patient is still in the hospital and followed up by clinic visit at 30 days after indexed PTA if the patient has been discharged from the hospital and every 6 months thereafter. If participants miss indicated clinic visits, study assistants will call or directly contact the participants or subjects’ family.

The primary endpoint is the composite major adverse cardiac event (MACE) on long-term follow-up. Pre-specified secondary endpoints include the MACE between the screening and 30 days after PTA, and the composite major coronary event on long-term follow-up. Other endpoints include death from any cause, congestive heart failure requiring hospitalization, and any coronary revascularization. The MACE includes cardiovascular death, non-fatal myocardial infarction, non-fatal stroke, and target vessel revascularization (any unplanned coronary vessel revascularization). The composite major coronary event includes fatal or non-fatal myocardial infarction, recurrent angina pectoris, and target vessel revascularization (any unplanned coronary vessel revascularization). The diagnosis of myocardial infarction and stroke has been previously described in detail [6]. Clinical follow-up will be performed 30 days after PTA and every 6 months until the end of the 1-year follow-up for the last randomly assigned participant. The follow-up schedule is listed in Table 2. All outcome data should still be collected for participants who discontinue or deviate from intervention protocols. The clear definitions of each component of primary and pre-specified secondary endpoints are provided to all assessors, and training of assessors to enhance the quality of measurements is performed on site initiation visit.

**Table 2 Tab2:** Follow-up schedule

	V0	Cath	PCI	CABG	PTA	V1	V2	V3	V4	V5	V6	V7	V8
Time elapse from PTA					0	30 (±7)D	24 (±2)W	48 (±2)W	72 (±2)W	96 (±2)W	120 (±2)W	144 (±2)W	168 (±2)W
CRF	001	002	003	004	005	006	007	008	009	010	011	012	013
Markers/SNPs/miRNAs					X								
CBC	X												
BCS	X												
BW/BH	X												
BP/HR	X					X	X	X	X	X	X	X	X
History and PE	X					X	X	X	X	X	X	X	X

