### Statistical analysis plan

To compare baseline characteristics between routine and selective strategy groups as well as the routine strategy group and the registration group, all interval-scaled variables will be presented as mean ± standard deviation. Skewed interval-scaled data will be reported as median (interquartile range). Categorical variables will be presented as frequency and proportion (percentage). Chi-squared or Fisher’s exact test will be used for comparison of categorical variables between groups, whereas Mann-Whitney *U* test or unpaired Student’s *t* test will be used for interval-scaled variables as appropriate.

To compare the endpoints between routine and selective strategy groups, each analysis will be performed by “intention-to-treat” and “per protocol”. Proportional or Fisher’s exact test will be used for analysis of the proportion of primary, secondary, and other endpoints between routine and selective strategy groups as appropriate. For primary endpoint, significantly greater than 5 % reduction of MACE in the routine strategy group compared with the selective strategy group will be analyzed. By using the same statistical methods, subgroup analysis will include comparison of the proportion of endpoints in subgroups of these two randomized arms, such as patients with critical limb ischemia (Rutherford classification of at least 4), chronic kidney disease (at least stage 3), end-stage renal disease, old age, different genders, tobacco smoking, diabetes mellitus, hypertension, hyperlipidemia, metabolic syndrome, anemia, bedridden, hypoalbuminemia, elevated high-sensitivity C-reactive protein level, and so on. Kaplan-Meier analysis will be used to study patient survival and event-free status by using the log-rank test (Cox-Mantel) to ascertain differences between groups. If more than one endpoint occurs within the follow-up period for assessing event-free status, only the first event will be used in the analysis. Generalized estimating equation will be used to address whether and how the clustering by centers. Missing data will be treated with the multiple imputation method.

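### Kaplan-Meier curves for MACE-free status would overstate absolute MACE risk in each arm, because about half of the expected deaths lie outside the endpoint

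*Protocol article*

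**What the plan says.** Four statements in the Protocol article bear on this.

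- **Endpoint** (Data collection and outcome measurement): "The MACE includes cardiovascular death, non-fatal myocardial infarction, non-fatal stroke", plus unplanned coronary revascularization. Death from a non-cardiovascular cause is not a component. All-cause mortality stands apart, in the list that begins "Other endpoints include death from any cause, congestive heart failure requiring hospitalization, and any coronary revascularization". The secondary coronary composite has fatal myocardial infarction as its only fatal component.
- **Time-to-event method** (Statistical analysis plan): "Kaplan-Meier analysis will be used to study patient survival and event-free status by using the log-rank test". The rule for multiple events is "If more than one endpoint occurs within the follow-up period for assessing event-free status, only the first event will be used in the analysis". The section names no cumulative-incidence method and does not say how a death outside the endpoint is handled.
- **Comparison of proportions** (Statistical analysis plan): "Proportional or Fisher’s exact test will be used for analysis of the proportion of primary, secondary, and other endpoints". The hypothesis of a reduction beyond 5 points, and the sample size, are framed on these proportions.
- **Expected mortality** (Background): "the average rate of total mortality is 25 % and the average rate of cardiovascular death is 12" per cent.

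**The concern.** Kaplan-Meier knows only events and censoring. A patient who dies of cancer or sepsis without a MACE cannot be counted as an event under the endpoint definition, so the ordinary reading is that this patient is censored on the day of death. The estimator then treats the patient like someone still alive and under observation, who may yet have a MACE. That is harmless when such deaths are rare. Here they are not, by the plan's own figures.

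What is at stake is the absolute risk that readers take from the curves. Follow-up runs from 1 to 3 years, so the Kaplan-Meier plot is where MACE risk at a given time would be read off. The proportion test counts the same patients as having had no MACE, so the two planned analyses of one endpoint describe different quantities.

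**Working it through.** **The plan's own figure first.** Inputs from Power estimation and sample size calculation: 40% versus 24%, margin 5 points, one-sided alpha 0.05, power 80%, dropout 4%.

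- n per arm = (1.645 + 0.842)² × (0.40×0.60 + 0.24×0.76) / (0.16 − 0.05)² = 6.18 × 0.4224 / 0.0121 ≈ 216
- Total 432; 432 / 0.96 = 450

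This reproduces 432 and 450 exactly. The sample size therefore rests on a comparison of proportions, with no Kaplan-Meier quantity in it.

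**Share of deaths outside MACE.** (25 − 12) / 25 = 13 / 25 = 52%.

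**Kaplan-Meier reading when these deaths are censored.** Let c1 be the true cumulative incidence of MACE and c2 that of non-cardiovascular death as first event. Assume constant hazards.

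- Total cumulative hazard: L = −ln(1 − c1 − c2)
- MACE part: L1 = L × c1 / (c1 + c2)
- 1 minus Kaplan-Meier: 1 − exp(−L1)

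The 13% cannot simply be taken as c2, because some of these deaths will follow a MACE. The range 5 to 13% is therefore an assumption.

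| c2, both arms | Selective (true 40%) | Routine (true 24%) | Difference (true 16.0) |
|---|---|---|---|
| 5% | L = −ln 0.55 = 0.598; L1 = 0.531; 41.2% | L = −ln 0.71 = 0.342; L1 = 0.283; 24.7% | 16.5 |
| 13% | L = −ln 0.47 = 0.755; L1 = 0.570; 43.4% | L = −ln 0.63 = 0.462; L1 = 0.300; 25.9% | 17.5 |

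If 13% is instead read as the net risk of non-cardiovascular death (the risk if MACE did not occur), the result is 42.6% versus 25.6%, a difference of about 17.0 points.

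**Unequal non-cardiovascular death.** Keep true MACE at 40% versus 24%.

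- 8% selective, 18% routine: L1 = 0.654 × 0.40/0.48 = 0.545, giving 42.0%; L1 = 0.545 × 0.24/0.42 = 0.311, giving 26.7%. The difference is 15.3 points, below the true 16.
- 18% selective, 8% routine: 45.0% versus 25.1%, a difference of 19.9 points.
- With 13% in the selective arm, the Kaplan-Meier difference falls to 16 when the routine arm reaches about 22%.

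**Log-rank test.** With these deaths censored, it tests equality of the cause-specific MACE hazards, which is a valid null hypothesis whatever the rate of other deaths. A simulation (216 per arm, follow-up uniform over 1 to 3 years, 5,000 runs, equal MACE hazards) gave two-sided rejection of 5.4% (one-sided 5.9%) with equal non-cardiovascular death. It gave 4.9% (one-sided 5.1%) with that hazard doubled in one arm. These are near nominal.

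**The case against.** The strongest reply is that the plan never says these deaths are censored. It speaks of patient survival and event-free status together, all-cause death is among its listed endpoints, and an article may leave censoring rules to a fuller document. One could also let any death end event-free status, and then nothing would be censored in this way. This stands in part: censoring is an inference, and the silence alone is no defect. But the method and the endpoint are both stated. Counting any death as an event would yield a curve for MACE or any death, which is not the MACE that the article defines.

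A second reply is that the shift is small. The standard error of the difference at 216 per arm is √(0.4224 / 216) = 0.044, or 4.4 points, against a shift of at most 1.5 in the range used. The 13% also comes from subtracting averages over unspecified intermediate or long follow-up. That is fair, and it is why this is only an improvement to a supporting analysis. The shift within an arm is nevertheless systematic, and it is avoidable.

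A third reply is that crude proportions and any time-to-event estimate would differ anyway, because follow-up varies. That also stands: the fix makes the curve estimate the actual risk of MACE by a given time, but it will not make it match the crude proportions.

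A reader might infer three stronger things, and the documents support none of them:

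- That the log-rank test is invalid. It is a proper cause-specific test.
- That the curves will necessarily exaggerate the gap between arms. This requires similar non-cardiovascular death in both arms.
- That success against the 5-point margin is at risk. The margin, the hypothesis and the sample size all rest on proportions.

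**Conclusion.** The point holds as a limited one about absolute risk. If deaths outside MACE are censored, 1 minus Kaplan-Meier overstates MACE risk in each arm whenever such deaths occur. Under constant hazards, true MACE of 40% versus 24%, and 5 to 13% first-event non-cardiovascular death per arm, the overstatement is 1.2 to 3.4 points in the selective arm and 0.7 to 1.9 in the routine arm. The difference is overstated by about 0.5 to 1.5 points when non-cardiovascular death is equal between arms. Its direction can reverse when it is not equal, as the 15.3-point example shows.

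The log-rank comparison, the primary proportion test, the margin and the sample size of 450 are untouched.

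**What to change.** For MACE and the coronary composite, show Aalen-Johansen cumulative incidence curves in place of 1 minus Kaplan-Meier, with deaths outside the endpoint as competing events. For MACE that means non-cardiovascular death. For the coronary composite it means any death other than fatal myocardial infarction. Label the log-rank test and any hazard ratio as cause-specific. Keep Kaplan-Meier for death from any cause, where it is the right estimator.

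The cost is a few sentences in the analysis plan, slightly more analysis work and possibly different software for this one analysis. No new data should be needed: the blinded endpoint committee already has to classify deaths in order to adjudicate MACE and fatal myocardial infarction.

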In this principal investigator-initiated prospective RCT, the PIROUETTE-PTA (Prognostic Impact of Routine Coronary Catheterization in Low Extremity Artery Disease Undergoing Percutaneous Transluminal Angioplasty) Study investigators will evaluate the prognostic effects of routine coronary angiography (routine strategy) versus selective coronary angiography based on the results of non-invasive stress tests (selective strategy) or conservative management (real-world strategy) before PTA for LEAD. The potential mechanisms will be elucidated. We hypothesize that a strategy of routine coronary angiography will positively impact long-term outcome as well as favorable cost-effectiveness, being superior to “selective strategy” or “real-world” strategy, in LEAD patients receiving PTA.

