### Blinding and randomization

Owing to the nature of the trial interventions, it will not be possible to blind the investigators at clinical trial sites, the participants, or the participants’ relatives. All other parties in the trial will be blinded. Those assessing biomarkers, single-nucleotide polymorphisms, micro-ribonucleic acids, and clinical endpoints are all blinded after assignment to interventions. Investigators conducting the statistical analyses will be blinded; the two intervention groups and one registry group will be coded as, for example, A, B, and C.

Eligible participants were randomly assigned to routine strategy or selective strategy by using unrestricted randomization and open label for allocation. Sealed envelopes for allocation concealment are provided. The allocation sequence is generated by [name]. Detailed information regarding the allocated group is given on cards contained in sequentially numbered, opaque, and sealed envelopes. These are prepared at the core coordinating center and kept in an appropriate location on each site. After enrollment of a participant, the appropriate numbered envelope is opened at the participating site. The information on whether the patient is to be a “routine” or “selective” case can be found on the card and this information then is given to the coordinator of the core coordinating center. Then, the investigator and research nurse follow the intervention protocol according to the allocation assignment. If participants are not willing to be randomly assigned, they will be included in the registration group if they agree. This information should also be given to the coordinator of the core coordinating center. The enrollment will be closed if the target number of randomly assigned participants is reached.

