### Power estimation and sample size calculation

As previously reported, the CARP (Coronary Artery Revascularization Prophylaxis) trial [13] shows a mortality of 23 % in the no-revascularization group, at a median of 2.7 years after randomization, and an incidence of MACE can be observed in 20 % of cases within 30 days after major vascular surgery. In addition, our previous study shows 25 % mortality, 8 % non-fatal myocardial infarction, 2 % non-fatal stroke, and 15 % coronary revascularization at a median of 10 months after PTA (total MACE rate is 35 %) [18]. Furthermore, a previous study showed that an absolute risk reduction of 16.7 % in MACE was observed in patients receiving routine coronary angiography versus selective group before major vascular surgery [6]. Therefore, we calculated that we would detect an absolute risk reduction of 16 % (estimated risk reduced from 40 % to 24 %) in primary composite events at long-term follow-up by enrolling a total sample of 450 patients (sample size of at least 432 with an estimated dropout rate of 4 %), with a one-sided alpha of 0.05, a power of 80 %, and a superior margin of 5 %. Although the superior margin is not absolutely necessary to demonstrate that the routine strategy is superior to the selective strategy, 5 % superior margin is to conservatively assess whether using the routine strategy would significantly reduce not only more but also at least 5 % greater in MACE than the selective strategy. The sample size would be smaller if there were no setup of the superior margin. Strategies for achieving adequate participant enrollment to reach the target sample size include selecting high-volume centers and interventionists for PTA and providing monetary incentives, which meet rigorous ethical requirements, to investigators and study staff for enrollment of participants.

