Although the main purpose of this study is not to compare the endpoints between the routine strategy group and the registration group or between randomized groups and the registration group, similar analyses as above will be performed to explore differences among patients in these groups. For all analyses, a *P* value of less than 0.05 is regarded as statistically significant. All statistical analyses are performed by using IBM SPSS Statistics 22.0 for Windows (IBM Corporation, Armonk, NY, USA), but the subgroup analysis is performed by using SAS software (Version 9.1.3; SAS Institute Inc., Cary, NC, USA).

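### The contrasts with the self-selected registration group use unadjusted tests at P < 0.05, although the Background hypothesises superiority over that group's real-world strategy

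*Protocol article*

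**What the plan says.** **Registration group.** Under Blinding and randomization, patients who refuse randomisation enter this group if they agree. Under Allocation and intervention, their care is usual care, settled between operators, patients and relatives. Participants and eligibility puts the group at about 250, beside 450 randomised.

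**Analysis.** The Statistical analysis plan section compares the randomised arms by a proportion or Fisher's exact test and by Kaplan-Meier curves with a log-rank test. It adds a GEE for clustering by centre and names no baseline covariates for it. For contrasts with the registration group, "similar analyses as above will be performed to explore differences among patients in these groups". The same sentence says that these contrasts are not the study's main purpose. The next sets P < 0.05 as significant for all analyses, without exception.

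**Hypothesis.** The Background states: "We hypothesize that a strategy of routine coronary angiography will positively impact long-term outcome". The sentence goes on to claim superiority over the selective strategy or the real-world strategy.

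**Randomised comparison.** Patients are allocated "by using unrestricted randomization and open label for allocation". The sample size rests on "estimated risk reduced from 40 % to 24" per cent, "with a one-sided alpha of 0.05", 80% power and "a superior margin of 5" percentage points, which gives a "sample size of at least 432 with an estimated dropout rate of 4" per cent.

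**The concern.** Both membership of the registration group and the care given in it are chosen. Willingness to be randomised, and the usual care that follows, may go with age, limb severity, renal disease or frailty. An unadjusted difference between the routine arm and this group therefore mixes any effect of strategy with case mix. The mixture can favour the routine strategy or hide a benefit.

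The article plans to compare baseline characteristics of the routine and registration groups, so measured imbalance will be seen. Nothing then carries it into the endpoint comparison.

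The Background hypothesis names the real-world strategy as a comparator, and no other group in the trial can stand for it. A P value below 0.05 from this contrast would meet the article's own criterion for significance, and could be reported as support for that hypothesis even if selection explained all of it.

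**Working it through.** **1. The plan's own figure (randomised arms).** Inputs from Power estimation and sample size calculation: 40% and 24%, margin 5 points, one-sided alpha 0.05, power 80%.

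- Variance term: 0.40 × 0.60 + 0.24 × 0.76 = 0.4224
- n per arm = 0.4224 × (1.645 + 0.842)² / (0.16 − 0.05)² = 215.8, so 216 per arm and 432 in total
- Dropout: 432 / 0.96 = 450

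Both stated figures reproduce from an unadjusted, unpooled test. The stated power does not depend on covariate adjustment.

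**2. Registration contrast.** Inputs: 225 routine patients (450 at 1:1) and 250 registration patients. Assumptions: no true effect, a common event rate of 40%, and one factor that raises event risk by 25 points and differs in prevalence by 15 to 20 points.

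- Bias = prevalence gap × risk effect: 0.15 × 0.25 = 0.0375 and 0.20 × 0.25 = 0.05
- SE = √[0.24 × (1/250 + 1/225)] = 0.045
- False-positive rate at two-sided 0.05 = 1 − Φ(1.96 − bias/SE) + Φ(−1.96 − bias/SE)
- Bias 0.0375 (bias/SE 0.83): about 13%
- Bias 0.05 (bias/SE 1.11): about 20%

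The documents give neither the imbalance nor the strength of any factor, so here is a wider range. The same formula is used, with risk 30% in the routine arm, 30% plus the bias in the registration group, and unpooled variances:

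| Prevalence gap | Risk effect | Bias | False-positive rate |
|---|---|---|---|
| 10 points | 10 points | 1 point | 5.6% |
| 10 points | 20 points | 2 points | 7.6% |
| 20 points | 20 points | 4 points | 15.5% |
| 30 points | 20 points | 6 points | 28.6% |
| 30 points | 30 points | 9 points | 54.5% |

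The bias does not depend on sample size, so enrolling more registration patients would not reduce it.

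**3. Randomised contrast: what adjustment could add.** SE at 216 per arm = √(0.4224/216) = 0.0442. If covariates explain a share R² of outcome variance (assumption), power = Φ[0.11 / (0.0442 × √(1 − R²)) − 1.645]:

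| R² | Power |
|---|---|
| 0 | 80.0% |
| 0.05 | 81.8% |
| 0.10 | 83.6% |
| 0.15 | 85.4% |

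**4. Is chance imbalance between the arms a bias?** For a factor with 50% prevalence, the SD of the between-arm difference is √(2 × 0.25/225) = 0.047, so the 95% range is ±9.2 points. With a 25-point risk effect this moves the estimate by up to 9.2 × 0.25 = 2.3 points. The unadjusted 95% half-width is 1.96 × 0.0442 = 8.7 points and already contains that variation. It is sampling error, not bias.

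**The case against.** **The contrast is exploratory.** The article sets it apart from the main purpose. The sample size and the closing Discussion rest nothing on the registration group. This stands, and it limits the consequence. It does not remove the confounding, exempt the contrast from the P < 0.05 rule or fit the Background hypothesis.

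**Adjustment may be in a fuller plan.** The word similar leaves some room, and an article often leaves model detail elsewhere. But the article is not silent: it names the methods to be carried over, and none uses patient-level covariates. The centre GEE does mean that the analysis is not wholly without modelling. It addresses clustering, not differences between patients who accept and who refuse randomisation.

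**The error rates are assumed.** This is so. They show what plausible imbalances would do and do not predict the trial's error rate.

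**Stronger readings that the documents do not support.** A reader might infer that unrestricted randomisation with an unadjusted test biases the primary result, because chance imbalance could shift it by a material part of the 5-point margin. That shift is already inside the valid standard error and does not raise the type I error. A reader might also infer that adjustment would rescue substantial power. The 50%-prevalent, 25-point factor explains about 0.25² × 0.25 / 0.24 = 6.5% of outcome variance, which takes power only to about 82%. The documents do not say how prognostic the candidate covariates are.

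**Conclusion.** The point holds for the registration contrasts. As written, the plan tests a self-selected, usual-care group against randomised patients without patient-level adjustment, applies a significance threshold, and has a stated hypothesis that only this comparison can address. Under the assumed 15- to 20-point prevalence gap and 25-point risk effect, the nominal 5% error becomes about 13% to 20%. Other assumptions give about 6% to 55%. The exploratory label keeps this from touching the trial's main conclusion, so it should be corrected but does not threaten the primary analysis.

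The randomised comparison contains no error on this point. Adjustment there would be an optional gain in precision whose size rests on an R² that the documents do not give.

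**What to change.** **Registration contrasts.**

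1. Estimate risk differences by propensity weighting (overlap or inverse-probability) or by covariate standardisation, using the baseline factors already named for subgroups in the Statistical analysis plan section, such as critical limb ischaemia, chronic kidney disease, end-stage renal disease, age and diabetes.
2. Report estimates with confidence intervals, label them as non-randomised, and exempt them from the P < 0.05 rule. Unmeasured selection will remain and should be acknowledged.
3. Remove superiority over the real-world strategy from the Background hypothesis, or mark it as exploratory.

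**Randomised comparison (optional).** Prespecify a covariate-standardised risk difference against the 5% margin, adjusted for a short list such as critical limb ischaemia, diabetes, chronic kidney or end-stage renal disease, and age. Say how it fits with the centre GEE, and report the unadjusted result beside it.

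**Cost.** Rewording and modest programming, including the work of combining standardisation with the planned multiple imputation. Recruitment and sample size do not change. The subgroup list implies that these covariates are recorded, but the case report form content is in an additional file that is not shown, so this should be confirmed.

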**Discussion:**

The results of the trial will, for the first time, support better decision-making for coronary evaluation before PTA in LEAD. If favorable, routine coronary angiography followed by revascularization will improve cardiovascular outcomes in LEAD patients undergoing PTA.

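### Five non-primary endpoints may each be declared significant at P<0.05 whatever the primary shows, with no gatekeeping and no exploratory label

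*Protocol article*

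**What the plan says.** The protocol article sets three tiers under Data collection and outcome measurement:

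- Primary: "The primary endpoint is the composite major adverse cardiac event (MACE) on long-term follow-up".
- Secondary: "Pre-specified secondary endpoints include the MACE between the screening and 30 days after PTA, and the composite major coronary event on long-term follow-up".
- Other: "Other endpoints include death from any cause, congestive heart failure requiring hospitalization, and any coronary revascularization".

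The Statistical analysis plan section then tests all three tiers in the same way: "Proportional or Fisher’s exact test will be used for analysis of the proportion of primary, secondary, and other endpoints between routine and selective strategy groups". It adds that "each analysis will be performed by “intention-to-treat” and “per protocol", and it provides Kaplan-Meier curves with log-rank tests as well. The requirement to show a reduction greater than 5 percentage points is attached to the primary endpoint alone. The section closes with one threshold for everything: "For all analyses, a *P* value of less than 0.05 is regarded as statistically significant".

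The only comparisons described as exploring differences are those that involve the registration group. No testing order, dependence on the primary or division of alpha is given for the secondary and other endpoints.

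**The concern.** The threshold sentence is a rule the article states, and it reaches every endpoint in the randomized comparison. Taken literally, a trial that misses its primary could still report a statistically significant difference on any of five further outcomes.

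Two features make this more than a formality here:

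- **Unequal hurdles.** The primary must beat a 5-point margin. The other five face an ordinary test of zero difference.
- **Overlap.** MACE to 30 days is an early window on the primary. The major coronary composite shares myocardial infarction and unplanned coronary revascularization with it. A chance result on either would look like support for the routine strategy just after the primary had failed to give it.

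At stake is what may be claimed beyond the primary. The primary test itself is not affected. The point concerns the endpoint family in the full randomized comparison, not the subgroups.

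**Working it through.** **The plan's own figure.** The article gives no familywise error figure. Its one design calculation covers the primary alone and reproduces. With 40% against 24%, margin 5%, one-sided alpha 0.05 and power 80% (Power estimation and sample size calculation):

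n per arm = [0.40×0.60 + 0.24×0.76] × (1.645 + 0.842)² / (0.16 − 0.05)² = 215.8, so 216 per arm and 432 in total. Then 432 / 0.96 = 450.

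So the alpha, power and margin were set for the primary only.

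**Inputs from the article.** Two secondary endpoints, three other endpoints, and P<0.05 for each.

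**Assumptions, not in the article.** No true effect on any endpoint, two-sided tests, one analysis per endpoint, and normal test statistics with a common correlation ρ between endpoints.

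**Independent tests.** The chance of at least one P<0.05 among k tests is 1 − 0.95^k:

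- k = 2: 1 − 0.9025 = 9.75%
- k = 5: 1 − 0.7738 = 22.6%

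Whatever the correlation, the upper bound for five tests is 5 × 0.05 = 25%.

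**Correlated tests.** Simulation with 500,000 to 1,000,000 draws, counting |z| > 1.96:

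| ρ | two secondaries | all five |
|---|---|---|
| 0 | 9.8% | 22.6% |
| 0.3 | 9.5% | 20.9% |
| 0.5 | 9.1% | 18.3% |
| 0.7 | 8.4% | 14.9% |
| 0.8 | 7.8% | 12.7% |

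**False results favouring the routine arm only** (z > 1.96, ρ = 0.5): 9.2% for five endpoints and about 4.5% for the two secondaries.

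**Sensitivity checks.**

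- *Sidedness.* The threshold sentence gives none. If each test were one-sided at 0.05, as in the sample size section, all false results would favour the routine arm. Five tests would give 22.7% at ρ = 0 and 16.7% at ρ = 0.5.
- *Without any coronary revascularization.* Four two-sided tests give 15.6% at ρ = 0.5 (18.5% at 0, 11.4% at 0.8).
- *Endpoints built from shared components.* Four sets of assumed event rates were tried: cardiovascular death 12%, other death 10% to 13%, myocardial infarction 8%, stroke 2% to 3%, unplanned revascularization 10% to 15%, planned revascularization 0% to 25%, angina 5% to 10%, heart failure 8% to 10%, and 20% to 50% of MACE falling by 30 days. It was also assumed that 35% of cardiovascular deaths are fatal infarctions, and that 40% of infarctions lead to unplanned revascularization and 40% of unplanned revascularizations come with angina. Components were otherwise independent. The implied correlations gave 20.9% to 22.0% for five endpoints and 9.2% to 9.6% for the two secondaries, inside the ranges in the table.

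**The case against.** The strongest reply is that this is an argument from silence. An article condenses a fuller plan, and the handling of secondary endpoints is commonly left to that plan. The tiers are themselves a hierarchy, only the primary is powered, only the primary has a success criterion, and P<0.05 is an ordinary per-test threshold.

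Part of this stands. The threshold is a per-test level and holds per test. A reader might infer that a promised 5% familywise rate is broken, but the article makes no such promise. A reader might also infer that a lone secondary result is meant to carry the trial's conclusion. The abstract's sentence, "If favorable, routine coronary angiography followed by revascularization will improve cardiovascular outcomes in LEAD patients undergoing PTA", is conditional on a favourable result and does not say which endpoint must be favourable. The main Discussion is softer still, saying only that the strategy may be better. Neither text says that a secondary can replace a failed primary.

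It is also fair that any coronary revascularization is a doubtful member of a no-effect family. Routine angiography finds lesions to treat, so that endpoint may differ between arms by design. Fisher's exact test on rare events would lower the rates somewhat. The intention-to-treat, per-protocol and log-rank repeats, not counted here, would raise them.

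What does not stand is that nothing is stated. The article has its own analysis section, which fixes one significance rule for all analyses and keeps exploratory wording for the registration group. A later hierarchy or exploratory label would have to qualify that sentence. Being called secondary or other marks a lower tier but does not stop a declaration of significance.

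**Conclusion.** The point holds in a limited form. The article lets each of the five non-primary endpoints be called significant at P<0.05 regardless of the primary, and it gives none of them an exploratory or supportive label.

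With no true effect, two-sided tests and a common correlation between 0.8 and 0, at least one such result appears in about 8% to 10% of trials for the two secondaries and about 13% to 23% for all five. About half of these favour the routine arm. The ranges rest on assumed correlations, and the five-endpoint figure also needs no true effect on any coronary revascularization. A single headline value within the range should not be quoted as if the article fixed it.

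The defect leaves the primary analysis intact. It concerns which further claims the trial may make, and it is worth correcting because the correction is cheap.

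**What to change.** In the Statistical analysis plan section, keep P<0.05 as the nominal per-test level. Add that the only confirmatory claim is the primary MACE test, by intention to treat, against the 5-point margin, at its stated alpha. Then choose one of these:

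- **(a) Gatekeeping.** Test the two secondaries only if the primary succeeds, by intention to treat, with one named test, at a stated alpha and sidedness. Use one pre-specified order chosen by the sponsor (for example the order in which the article lists them), and stop at the first non-significant result.
- **(b) Labelling.** Describe the two secondaries as supportive.

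Under either option, report all-cause death, heart-failure hospitalization and any coronary revascularization as exploratory, and likewise the per-protocol and log-rank repeats. Give estimates with 95% confidence intervals and no declaration of significance.

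This is a wording change to make before unblinding; the article reports that recruitment was still open. It needs no extra patients, visits or data. The price is that a secondary P<0.05 cannot be claimed as confirmatory if the primary fails.
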